## Abstract

**Background:**

Robot‐assisted radical prostatectomy (RARP) is the standard surgical procedure for the treatment of prostate cancer. RARP requires a trade‐off between performing a wider resection in order to reduce the risk of positive surgical margins (PSMs) and performing minimal resection of the nerve bundles that determine functional outcomes, such as incontinence and potency, which affect patients’ quality of life. In order to achieve favourable outcomes, a precise understanding of the three‐dimensional (3D) anatomy of the prostate, nerve bundles and tumour lesion is needed.

**Study Design:**

This is the protocol for a single‐centre feasibility study including a prospective two‐arm interventional group (a 3D virtual and a 3D printed prostate model), and a prospective control group.

**Endpoints:**

The primary endpoint will be PSM status and the secondary endpoint will be functional outcomes, including incontinence and sexual function.

**Patients and Methods:**

The study will consist of a total of 270 patients: 54 patients will be included in each of the interventional groups (3D virtual, 3D printed models), 54 in the retrospective control group and 108 in the prospective control group. Automated segmentation of prostate gland and lesions will be conducted on multiparametric magnetic resonance imaging (mpMRI) using ‘AutoProstate’ and ‘AutoLesion’ deep learning approaches, while manual annotation of the neurovascular bundles, urethra and external sphincter will be conducted on mpMRI by a radiologist. This will result in masks that will be post‐processed to generate 3D printed/virtual models. Patients will be allocated to either interventional arm and the surgeon will be given either a 3D printed or a 3D virtual model at the start of the RARP procedure. At the 6‐week follow‐up, the surgeon will meet with the patient to present PSM status and capture functional outcomes from the patient via questionnaires. We will capture these measures as endpoints for analysis. These questionnaires will be re‐administered at 3, 6 and 12 months postoperatively.

Abbreviations2Dtwo‐dimensional3Dthree‐dimensionalmpMRImultiparametric MRINVBneurovascular bundlePSMpositive surgical marginRARProbot‐assisted radical prostatectomy

## Background

Prostate cancer is the most common cancer in the United Kingdom, affecting one in eight men and causing the death of over 11 500 men per year [1]. Specifically, in 2020, the worldwide prostate cancer incidence, mortality and 5‐year prevalence were 14.1%, 6.8% and 20%, respectively [2].

Robot‐assisted radical prostatectomy (RARP) is the standard surgical approach to treat prostate cancer. Cancer extending beyond the prostate capsule increases the risk of positive surgical margins (PSMs), which are independent predictors of prostate cancer and biochemical recurrence after RARP [3]. RARP requires a trade‐off between performing a wider resection in order to achieve low PSM rates (11%–37% on average [4, 5]), and performing a narrower resection to preserve structures that determine functional outcomes, such as incontinence and potency, which affect patients’ quality of life [6]. Urinary incontinence remains one of the most troublesome postoperative complications, with aetiology that is complex, multifactorial, and affected by surgical technique, surgeon's skill and patient characteristics [7]. Erectile dysfunction is of particular concern after RARP, with prevalence varying from 14% to 90% [8].

Multiparametric MRI (mpMRI) is increasingly used to support the diagnosis, tumour localisation, and management of prostate cancer through three‐dimensional (3D) T2‐weighted imaging, diffusion‐weighted imaging with apparent diffusion coefficient, and dynamic contrast‐enhanced sequences [9]. mpMRI is also used by surgeons for surgical planning since a good understanding of the anatomy is essential to reduce the risk of complications. However, surgeons are expected to mentally reconstruct conventional two‐dimensional (2D) mpMRI into a 3D representation that matches the anatomy as seen through an endoscope during RARP [10]. Precise knowledge of the 3D location of the tumour and its relationship to the prostate capsule and neurovascular bundles (NVBs) can inform the surgical management and nerve‐sparing technique, whilst reducing PSMs [11, 12]. Although studies have shown that mpMRI induces surgeons to change their surgical plan, reducing PSMs [13], it is difficult for surgeons to imagine intra‐operatively the precise location of tumours entirely from preoperative multiparametric medical images, a process that becomes less challenging with experience.

Some methods have been proposed to support the understanding of a patient's anatomy during surgery. 3D surgical navigation models have been displayed next to the surgeon console [12], overlaid on endoscopic videos using elastic‐based augmented reality [11], and made available to surgeons as 3D printed models during surgery [14]. Despite the variability reported in these studies, evidence from a recent literature review and meta‐analysis [15] suggests a trend towards a reduction in PSMs [11, 12, 14], with no clear evidence of the impact on functional postoperative outcomes. That review and meta‐analysis of the potential benefits of 3D models highlighted limitations in current studies, including a lack of comparison between 3D printed and virtual models, lack of description and justification for the methodology chosen, and studies contradicting each other. Moreover, the role of 3D virtual and 3D printed models in surgery is yet to be defined as there are many covariates that have an effect on outcomes, such as surgeon's expertise, location of cancer lesions, number of anatomical structures to be included, approaches for the creation of 3D models, among others.

### Study Design

This is the design for a single‐centre parallel feasibility study consisting of two prospective intervention arms (a 3D printed model and a 3D virtual model), and a retrospective and a prospective control group (Fig. 1). Although this study will be non‐blinded for surgeons as they will be operating on patients using either of the models, it will be blinded for analysis. Note that this will not be a randomised study.

**Fig. 1 bju16850-fig-0001:**
[figure not shown]
Flow of participants and execution of our feasibility study. RARP, robot‐assisted radical prostatectomy.

The aim of this study is to measure the effect of 3D models on the reduction of PSM rates and on functional outcomes after RARP. Our main hypothesis is that there will be a reduction of positive resection margins (PSMs) and improvement of functional outcomes for patients undergoing RARP when surgeons are presented with a 3D printed or 3D virtual patient‐specific prostate model during surgery. Specifically, we hypothesise that 3D models reinforce the mental reconstruction of the anatomy that surgeons acquire via conventional 2D mpMRI whilst assisting surgeons in matching the precise location of the anatomy and lesions with respect to the endoscopic view they observe during RARP [10]. 3D models could inform the surgical management and nerve‐sparing technique, whilst avoiding increases in PSM rates. Studying both 3D virtual and 3D printed models will allow us to understand whether tactile information is important. We highlight the importance of recruiting surgeons across different levels of expertise to reduce bias and avoid having expertise as a confounder for the impact of 3D models on the reduction of PSMs. Therefore, we will stratify our results based on each surgeon's number of years of experience.

We will also report measures related to the deployment of this feasibility study in anticipation of a subsequent larger randomised controlled trial. Measures include patient recruitment rate, and percentage of cases that led to successful model deployment in the operating theatre.

### Endpoints

The primary study outcome is PSM rates measured after specimen analysis. Secondary outcomes include incontinence rates (pad weights, electronic Patient‐Reported Outcome Measures), erectile dysfunction (International Index of Erectile Function score, and Erectile Hardness Score), and International Consultation on Incontinence Questionnaire‐Urinary Incontinence (ICIQ‐UI) score captured at 3 months after surgery. Other secondary outcomes are related to our pipeline deployment metrics, including patient recruitment rate and percentage of cases that led to successful model deployment in the theatre.

### Eligibility Criteria

Men will be included in the study provided they meet the following criteria:
T2–T3a prostate cancer lesions located on the capsule and near NVBs;Gleason score ≥3 + 4; andEligibility for RARP after assessment of mpMRI during multidisciplinary team meetings according to local guidelines.

If any of the following criteria are met, the subject must not be included in the study:
Prior treatment for prostate cancer;Pre‐existing erectile dysfunction;Pre‐existing urinary incontinence;mpMRI not possible, or assignment to other research studies where functional outcomes are likely to change; orPresence of anterior tumour lesions of the prostate and those confined to the prostate.

## Methods

### Interventions

Patients diagnosed with prostate cancer will undergo discussion at the weekly multidisciplinary team meeting at Guy's Hospital (London, UK) to decide management options. These patients will then be followed up in the clinic to determine those who opted for RARP. A list of those scheduled for RARP in the upcoming months will be collected. Patients will fill out questionnaires in the clinic regarding baseline functional information preoperatively related to potency and continence and these data will be stored on REDCap (Research Electronic Data Capture software). The hospital electronic health record will be used to collect data on patient demographics, staging, Gleason score, prior treatment for prostate cancer, potency and incontinence to eliminate patients not meeting our inclusion criteria.

Patients will then be contacted via telephone and informed about the study. They will be given written information via e‐mail or in person preoperatively on: (i) the aims of the study; (ii) the patient information materials available; and (iii) contact details of chief investigator.

Patients can consent verbally to participate in the study via telephone but can opt to withdraw any time before the surgery. They will then be given a written consent form to sign before their surgery, which will include permission to use their data. Pseudo‐anonymisation will be carried out by a Clinical Research Fellow to allow data processing and analysis by Data Scientists.

Once patients have consented verbally, mpMRI will be obtained and anonymised for extraction of anatomical structures. Histology data will also be collected from previous prostate biopsy to help better identify the exact location and size of lesions. These will then be reviewed by the radiologist to guarantee the patient is eligible given our inclusion criteria.

#### Segmentation of Anatomy on mpMRI

The radiologist will delineate a total of five different prostate‐related anatomical regions on mpMRI using ‘3D Slicer’, a process commonly referred to as image segmentation. First, automated segmentation of the prostate gland will be carried out using ‘AutoProstate’ in MONAI Labels on axial T2‐weighted images [16, 17]. Typical parameters of acquisition of T2‐weighted imaging include slice thickness = 3.5 mm, interslice gap = 3.5 mm, and field of view = 180 mm * 180 mm. The results of prostate segmentation will be validated by the radiologist, and, if necessary, manually corrected. Then, manual segmentation of cancer lesions will be performed on T2‐weighted, apparent diffusion coefficient, and high b‐value diffusion weighted image sequences supported by histological data and patient records. Last, the external sphincter, urethra, and NVBs will be manually segmented on T2‐weighted images (Fig. 2 top and Fig. 3 left).

**Fig. 2 bju16850-fig-0002:**
[figure not shown]
Two‐arm parallel study. Top: muliparametric MRI (mpMRI) is used to construct three‐dimensional (3D) printed or 3D virtual patient‐specific prostate anatomical models preoperatively. Middle: a prospective control cohort and two prospective intervention arms, in which 3D printed or 3D virtual models are given to surgeons during robot‐assisted radical prostatectomy (RARP). Bottom: collection of postoperative surgical outcomes including PSMs and functional outcomes related to erectile dysfunction and urinary incontinence.

**Fig. 3 bju16850-fig-0003:**
[figure not shown]
Left: segmentation of patient‐specific prostate anatomy on multiparametric MRI (mpMRI) to extract annotations of the prostate gland (shown in translucent white), tumour lesions (shown in red), external sphincter (shown in purple), urethra (shown in yellow), and neurovascular bundles (shown in blue and green). Right: annotations resulting from segmentations are three‐dimensional (3D) printed and scanned using a coordinate measuring machine that captures a 3D representation of the physical model. The overlapping of annotations (in pink) and scanned 3D representation (in blue) validates that 3D printed models and 3D virtual models fully correspond to each other.

#### Surface Model Generation

Labels resulting from segmentation will be processed through a pipeline specifically developed for our study. This pipeline will create labels either for 3D virtual models or for 3D printing.

Patients will be assigned to one of the intervention groups based on the resources available to produce 3D printed or 3D virtual models in a timely manner before surgery (Fig. 2). Specifically, the allocation to an intervention arm will be carried out based on the time that the anonymised data are received by the engineering team and the remaining days before surgery to allow the generation of 3D models. Note that virtual models are faster to generate compared to printed models.

#### Control Group

Patients will be prospectively assigned to a control arm according to our inclusion/exclusion criteria. We aim to include cases following 1:2 propensity‐score matching with respect to intervention arms. These cases will be pseudo‐anonymised and data collected will include patient demographics, mpMRI, PSM status, and functional outcomes. For comprehensiveness, we also aim to include retrospective cases observed over the same period of time as the execution of our feasibility study, according to our inclusion/exclusion criteria. This prospective vs retrospective analysis will allow us to measure for any possible bias and validate whether the intervention arms have impact in comparison with historical data. A search for retrospective cases will be conducted over the same period of time as the execution of our feasibility study to reflect similar practice. However, given that bias might be introduced due to the nature of a retrospective arm, we will additionally include cases as part of a prospective control arm during the execution of our study, but only if there are enough cases after interventional arm assignments.

#### 
Three‐dimensional Printed Intervention Arm

Patients will be prospectively recruited to obtain 3D printed models to surgeons at the start of RARP. These models will be printed by Guy's and St Thomas' Hospitals 3D printing facilities, using an Object500 Connex1 polyjet 3D printer (Stratasys, USA). As part of the design of this protocol, we have developed a bespoke additive manufacturing workflow to meet the requirements of our patient‐specific 3D printing task. The aims of our workflow are: (i) to maximise the clarity with which tumour lesions can be discriminated from healthy glandular tissues, and (ii) to minimise geometrical deviation from the virtual model obtained from segmentation on mpMRI. Our workflow meets these ambitions by leveraging multiple materials (with visually contrasting properties) and multi‐part assembly (to eliminate the need for abrasive post‐processing). The geometrical accuracy of the following patient‐specific 3D printing specification was validated using a coordinate measuring machine (Faro, USA): disagreement between 3D printed and virtual surfaces (see Fig. 3, right panel).

We will print the healthy glandular tissue using a transparent photopolymer (VeroClear FullCure810), with an optically contrasting, opaque, white photopolymer (VeroWhitePlus FullCure835) to identify lesions. Furthermore, we have chosen to print the models in two approximately hemispherical sections (see Fig. 2 middle), the ‘overhang‐free’, monotonic geometry of which minimises the supporting material required. This is beneficial, eliminating the need for the abrasive polishing that risks undue deviation from the intended geometry, and that would otherwise be required to remove vestiges of supporting material to ensure gland transparency. To discriminate the NVBs and external sphincter from the remaining anatomy, we will use a distinct, soft photopolymer (Agilus30 Clear FLX935). The urethra will be demonstrated as a hollow passage through the gland. To ensure models can be traced to specific patients, the pseudo‐anonymised case identifier will be 3D printed (as a recessed label) into the surface of the gland, taking an inconsequential location remote from disease. Following printing, the two hemispheres will be combined using metallic pins, sized to ensure a reversible push‐fit. The sphincter will be held in place using an epoxy adhesive.

The design chosen for this study is the result of an iterative process resulting in 3D models printed in two halves that are easily put together with the aid of two metallic pins to allow the visualisation of urethra and cancer lesions. A pseudo‐anonymised code is automatically engraved into the prostate. The 3D models are printed in three different materials: prostate gland in translucent (VeroClear FullCure810), cancer lesions in white colour (VeroWhitePlus FullCure835), and external sphincter and NVBs in soft material (Agilus30 Clear FLX935), with the urethra showing as hollow.

#### 
Three‐dimensional Virtual Intervention Arm

Patients will be prospectively recruited to provide 3D virtual models to surgeons at the start of RARP via a laptop (Windows 10 Dell Latitude 3520). Pseudo‐anonymised T2‐weighted images and labels will be uploaded to Innersight Labs, a CE‐marked surgical planning tool, to visualise the prostate anatomical regions in 3D in theatre.

During RARP, a patient‐specific 3D printed or 3D virtual model will be available to the surgeon, who will be able to manipulate it at any time as a reference for the anatomy seen in the endoscopic video during robot‐assisted surgery. Videos currently recorded for RARP as standard practice will be used for analysis of the phases and actions performed during surgery to understand the relationship of the 3D printed/virtual model.

We will ask surgeons to complete a questionnaire after surgery to capture their perspectives in relation to the 3D models made available to them.

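### As written, the propensity matching is attached to the prospective controls only, so both comparisons that use the retrospective controls can mix case mix with the effect they are meant to show

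*Protocol article*

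**What the plan says.** All of the following comes from the protocol article; no full protocol or SAP is shown.

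- **Prospective controls.** In the Control Group section, directly after the sentence on prospectively assigned controls: "We aim to include cases following 1:2 propensity‐score matching with respect to intervention arms".
- **Retrospective controls.** The same section then adds, for comprehensiveness, "retrospective cases observed over the same period of time as the execution of our feasibility study, according to our inclusion/exclusion criteria". No matching or weighting is mentioned for them.
- **Their purpose.** "This prospective vs retrospective analysis will allow us to measure for any possible bias and validate whether the intervention arms have impact", the latter against what the section calls historical data.
- **Acknowledged weakness.** The section grants that a retrospective arm may bring bias. Its remedy is to add prospective controls, "but only if there are enough cases after interventional arm assignments".
- **Sizes.** The abstract gives "54 in the retrospective control group and 108 in the prospective control group", and "54 patients will be included in each of the interventional groups".
- **Analysis.** Data Analysis plans a Pearson chi-squared test of PSM across two intervention groups and one control group, without saying which control group is meant. An ANCOVA appears only for continuous questionnaire outcomes. Study Design adds stratification by surgeon experience and states that the study is not randomised.

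**The concern.** The retrospective group is given two tasks, and each needs it to be comparable with the group it is set against.

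- **Intervention arms against retrospective controls.** This is meant to confirm that the models work. If the retrospective cases carry more high-risk disease than the arms, the models look beneficial with no true effect. If they carry less, a real benefit is hidden.
- **Prospective against retrospective controls.** This is meant to show bias from retrospective collection. If one group has been selected to resemble the intervention arms and the other has not, a gap may be case mix and not collection bias. Agreement may mean that the two cancel.

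The protocol itself treats case mix as important: its Background lists surgeon expertise and lesion location among the covariates that affect outcomes, and it plans matching for the prospective controls. The stated criteria narrow the mix but still span T2 to T3a and Gleason 3+4 upwards.

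**Working it through.** **1. What the group sizes show.** The sizes add up as stated: 54 + 54 + 54 + 108 = 270. They do not settle which group is matched:

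- 108 prospective controls to 54 patients in one arm is 2 to 1; to both arms pooled (54 + 54 = 108) it is 1 to 1.
- 54 retrospective controls to 54 in one arm is 1 to 1; to 108 pooled intervention patients it is one control to two intervention patients, which could also be called 1:2.

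The reading that only the prospective controls are matched therefore rests on the order of the sentences, not on the counts.

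**2. Whether anything else balances the retrospective cases.** For PSM, nothing stated does. The eligibility criteria restrict the range but do not equalise the mix within it. The chi-squared test has no covariates. The ANCOVA does not cover PSM. The stratification covers surgeon experience only.

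**3. Size, as an illustration only.** The document gives neither stratum-specific PSM rates nor stratum shares. Assumptions:

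- There is no true effect of the models and no collection bias.
- There are two strata with PSM of 11% and 37%. These are the ends of the range in the Background, borrowed as stratum rates.
- 35% of the intervention arms and matched controls are high-risk. This is chosen so that PSM is 0.11 + 0.26 × 0.35 = 0.201, close to the roughly 20% expected in Sample Size Determination.
- The retrospective group has *d* more high-risk cases.

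Shift in PSM = *d* × (0.37 − 0.11) = 0.26 × *d*. With *d* of the opposite sign, the shift has the same size and the opposite direction.

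| *d* (points) | Retrospective PSM | Spurious shift | False rejection, 54 vs 108 | False rejection, 54 vs 54 |
|---|---|---|---|---|
| 10 | 22.7% | 2.6 points | 6.0% | 5.1% |
| 20 | 25.3% | 5.2 points | 12.0% | 9.4% |
| 30 | 27.9% | 7.8 points | 20.8% | 15.5% |

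False rejection is for a two-sided 5% test, in the direction of the shift, against a nominal 2.5%. The formula is Φ((shift − 1.96 × SE₀)/SE₁), with SE₀ pooled and SE₁ unpooled. For *d* = 30 and 54 vs 108:

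- pooled rate = (54 × 0.279 + 108 × 0.201)/162 = 0.227
- SE₀ = √(0.227 × 0.773 × (1/54 + 1/108)) = 0.0698
- SE₁ = √(0.279 × 0.721/54 + 0.201 × 0.799/108) = 0.0722
- Φ((0.078 − 0.1369)/0.0722) = Φ(−0.815) ≈ 0.208

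**4. Precision of the comparisons.** At 20% PSM the 95% half-width is 1.96 × √(0.16/54 + 0.16/108) = 13.1 points for 54 vs 108, and 1.96 × √(2 × 0.16/54) = 15.1 points for 54 vs 54. The data could not tell a case-mix shift of 3 to 8 points from an effect of retrospective collection.

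**5. Yardstick.** The one statistically significant study cited in the Discussion reported 25% against 33%, a difference of 8 points.

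**The case against.** **The text is ambiguous and condensed.** The matching sentence stands under one heading for all controls. The eligibility phrase is used for both control groups, so it does not by itself show two entry rules. A full protocol or SAP may match or adjust the retrospective cases. This is fair, and it limits the point to the article as written. It does not remove it, because the article states an inference that the described construction does not secure. If matching was meant to cover both groups, the same sentence settles that.

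**The groups may not differ at all.** A reader might infer that the two control groups differ by construction. The document does not support that. Matching makes them differ only if the intervention patients differ from the eligible pool. Both control groups share criteria, period and centre, and allocation between the two intervention arms depends on lead time, not on any stated tumour feature. This stands: the groups may differ, and no more can be said.

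**The size is assumed.** This also stands. A reader could reach larger shifts with more extreme inputs. For example, strata at 10% and 40% PSM with high-risk shares of 70% against 40% give 0.3 × 0.30 = 9 points. But they imply 0.3 × 10% + 0.7 × 40% = 31% PSM in the matched set, against the protocol's 20%, so that figure should not be used.

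**The comparison is supplementary and imprecise.** The retrospective cases are added for comprehensiveness, and the abstract's study design mentions only a prospective control group. With half-widths of 13 to 15 points, balancing would often leave the conclusion unchanged. That lowers the severity. It does not make an unbalanced comparison able to do the two tasks set for it.

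**Conclusion.** The point holds in a limited form. Followed as written, the plan sets a retrospective group with no stated balancing against the intervention arms and against the prospective controls, which are to be matched to those arms. It expects the first comparison to "validate whether the intervention arms have impact in comparison with historical data" and the second to reveal bias. Neither can be relied on to separate the intended effect from case mix.

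The size is not computable from the document. The 2.6 to 7.8 points rest on the borrowed 11% and 37% strata and an assumed imbalance of 10 to 30 points; the sign could be either. The upper end is close to the 8-point difference in the cited study.

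A reader might infer that the primary result is biased. The document does not show this. It would follow only if the retrospective group is the single control group in Data Analysis, or is pooled into it. The article does not say, and the condition on recruiting prospective controls leaves the possibility open. Severity is minor to moderate.

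**What to change.** State in the Control Group section that the retrospective cases are weighted or matched to the intervention arms with the same propensity model and the same pre-operative covariates as the prospective controls. State also that the comparison of the arms with the retrospective group, and that of the two control groups, are both made in those weighted or matched samples. If this was already intended, say so there.

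The cost is a sentence or two, one further run of the model and some loss of effective sample size. The loss cannot be predicted because the size of the retrospective pool is not given: matching from a small pool could drop many cases, and from a large one none. Weighting would keep all 54 cases in the analysis, though with a smaller effective number where the weights are uneven.
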